## Abstract

Strongyloidiasis affects an estimated 600 million people worldwide, especially in tropical and subtropical areas. Single-dose ivermectin treatment has shown to be effective among immunocompetent patients with uncomplicated strongyloidiasis. Here, we present the protocol of the ImmunoStrong study, a prospective observational study aiming to evaluate the effectiveness and safety of a single-dose ivermectin for treatment of uncomplicated strongyloidiasis in immunosuppressed patients. The secondary objectives are to assess accuracy of molecular techniques for the follow-up of these patients and to determine the population pharmacokinetics of ivermectin. The information retrieved by this study will cover relevant information gaps in the strongyloidiasis management among immunosuppressed patients.

## 1. Introduction

Human strongyloidiasis caused by the nematode *Strongyloides stercoralis* affects an estimated 600 million people worldwide, especially in tropical and subtropical areas [1]. Until now, scarce efforts have been made to reduce its prevalence. However, the World Health Organization has recently included strongyloidiasis among the targets for 2030 soil-transmitted helminth (STH) control [2]. 

Most of the patients with *S. stercoralis* infection are asymptomatic or present with mild symptoms in the form of gastrointestinal disturbances (abdominal pain, diarrhea, vomiting), respiratory symptoms (cough, dyspnea), and skin lesions (rash, larva currens) [3]. This parasite can persist in the host indefinitely in the absence of reinfections thanks to its ability to autoinfect the human host. Under immunosuppressive conditions such as corticosteroid therapy, solid organ transplantation, or human T lymphotropic virus 1 (HTLV-1) infection, its cycle of autoinfection can be amplified, leading to severe clinical presentations with high mortality, such as *Strongyloides* hyperinfection syndrome and disseminated strongyloidiasis [4,5]. 

Autochthonous cases of trongyloidiasis in Western European countries have been described, although they are currently anecdotal, restricted to specific areas, and mostly affecting elderly males who worked in agriculture in the past [6,7,8]. However, due to migratory flows and the increase in international travels in recent decades, strongyloidiasis is increasingly diagnosed outside endemic areas [9]. A recent review of the literature showed a prevalence of *S. stercoralis* infection ranging from 10% to 20% in immigrant population living in Spain. These data support the active screening of populations coming from endemic areas given the potential risk of serious presentation in situations of immunosuppression [10]. The frequency of this parasitosis and its potentially deleterious consequences has led the European Center for Disease Control to include strongyloidiasis in the routine screening of migrants coming from endemic areas [11].

The current therapeutic arsenal for the treatment of strongyloidiasis is basically limited to two drugs: Ivermectin and albendazole. There are few clinical trials that have evaluated the efficacy of these drugs for the treatment of strongyloidiasis, showing a cure rate of 76–98% for ivermectin and of 38–78% for albendazole. A recent meta-analysis comparing the efficacy of ivermectin versus albendazole showed the superiority of ivermectin, with ivermectin being the treatment of choice for strongyloidiasis [12]. Ivermectin, discovered in 1970 by the Japanese Nobel laureate Satoshi Omura, is one of the most widely used antiparasitic drugs in both human and animals. Its mechanism of action is not yet exactly known, and it has “in vitro” activity against various helminths (*S. stercoralis*, *Trichuris trichiura*, hookworms, different species of filarial worms, *Gnathostoma* sp), ectoparasites (lice, scabies), virus (dengue, the novel SARS-CoV-2), and mosquitoes (of the genus *Anopheles*) [13]. The duration of ivermectin treatment for strongyloidiasis was a matter of debate until a few years ago. However, a recent randomized clinical trial conducted in a nonendemic area (Strong Treat 1 to 4) compared a single dose of ivermectin (200 mcg/kg/day) versus four doses (a dose of 200 mcg/kg/day given for 2 consecutive days, and another two doses given 14 days apart), with a 12-month follow-up using classical parasitological tests, *S. stercoralis* serology, and detection of *S. stercoralis* DNA through polymerase chain reaction (PCR). The results showed that there were no differences between the two regimens (efficacy 86% versus 85% respectively, *p* = 0.75). Furthermore, similar cure rates were observed at 6 and 12 months after treatment [14]. Immunosuppressed patients were not included in this clinical trial. Thus, a lack of evidence about the efficacy of the single-dose regimen remains for this population.

The aim of the ImmunoStrong Study is to evaluate the effectiveness and safety of a single-dose ivermectin for the treatment of uncomplicated strongyloidiasis in immunosuppressed patients.

## 2. Methods

The ImmunoStrong Study is a prospective observational study where adult immunosuppressed (IS) patients with uncomplicated strongyloidiasis will be included. Control group will be composed by immunocompetent (IC) patients with uncomplicated strongyloidiasis. The study will be carried out in 8 sites in Spain and Italy: Vall d’Hebron University Hospital (Barcelona, Spain), Germans Trias I Pujol University Hospital (Badalona, Spain), Ramón y Cajal University Hospital (Madrid, Spain), La Paz-Carlos III University Hospital (Madrid, Spain), 12 de Octubre University Hospital (Madrid, Spain), Vega Baja Hospital (Orihuela, Spain), General University Hospital of Valencia (Valencia, Spain), and IRCCS Ospedale Sacro Cuore-Don Calabria (Negrar, Italia). The Parasitology Reference and Research Laboratory of the National Microbiology Center of the Carlos III Health Institute (ISCIII, Madrid, Spain) will perform the molecular diagnosis techniques.

### 2.1. Patient Eligibility

Inclusion criteria will include: Adult patients (≥18 years old) who sign the informed consent, diagnosis of strongyloidiasis either by direct parasitological methods (positive coproparasitological examination and/or agar plate culture) or by positivity of a serological technique (ELISA) with an optical density (OD) index greater than or equal to 2, and current residence in an area without evidence of active transmission of strongyloidiasis. The exclusion criteria will be as follows: Pregnancy or lactation, intolerance or allergy to ivermectin, renal failure (glomerular filtration rate equal to or less than 30 mL/min) or advanced liver disease (Child-Pugh B or C), coinfection by *Loa loa* (due to the risk of presenting encephalopathy when administering ivermectin), complicated strongyloidiasis (*S. stercoralis* hyperinfection syndrome or disseminated strongyloidiasis), planned trip to an area with evidence of active transmission of strongyloidiasis during the next 6 months (to avoid possible reinfections), and previous treatment with ivermectin (in the last year before inclusion).

Patients included in the IS group will be defined by presence of any of the following conditions at enrollment: Treatment with corticosteroids at a cumulative dose greater than or equal to 20 mg/day of prednisone (or equivalent) for at least 10 days, treatment with cytotoxics drugs or antimetabolites, bone marrow or solid organ transplantation, biological drugs, active solid or hematological neoplasia, HIV infection with CD4 lymphocyte count below 200 cells/mm^3^. On the other hand, patients included in the IC group must not have any of the previous conditions (and no HIV infection regardless of the CD4 lymphocyte count).

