### 2.2. Outcomes

The primary outcome will be noninferiority of the cure rate of immunosuppressed patients compared to immunocompetent patients. Cure rate is defined as the proportion of patients with a negative direct parasitological test and negative *S. stercoralis* serology or decrease of at least 50% of OD index at 6 months after treatment administration. We used a noninferiority margin of 14% to assess the primary outcome (i.e., lower bound of the 1-sided 95% CI of the difference between cure rates in immunosuppressed versus immunocompetent patients was no more than –14%). The secondary objective will be to compare the safety and tolerability of single dose ivermectin for the treatment of uncomplicated strongyloidiasis between immunosuppressed and immunocompetent patients. Three sub-studies have been prespecified: Evaluation of the usefulness of *S. stercoralis* PCR in feces in the follow-up after treatment of uncomplicated strongyloidiasis in adult patients (proportion of patients with negative *S. stercoralis* PCR after treatment compared to proportion of patients that fulfill the cure criteria),Determination of the population pharmacokinetics (PK) of ivermectin in a single dose for the treatment of uncomplicated strongyloidiasis in adult patients, andCreation of a repository of serum and stool samples from adult patients (immunosuppressed and immunocompetent) with uncomplicated strongyloidiasis (samples before and after treatment with ivermectin) for later use in the evaluation of new diagnostic tools or biomarkers.

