### 2.3. Study Protocol

Patients who meet the inclusion criteria will be invited to participate in the study and will be asked to sign the informed consent. All patients must have a coproparasitological study, a *Strongyloides* specific culture, and a *S. stercoralis* serology performed at baseline. The initial evaluation will include: Full blood cell count, basic biochemistry (glucose, kidney function, and liver profile), HIV serology, and detection of microfilaria in peripheral blood to screen for loiasis in patients coming from endemic areas. In addition, a serum sample (for sample repository), a fresh stool sample (for sample repository and *S. stercoralis* PCR), and a plasma sample (for pre-dose ivermectin population PK) will be collected and stored at −80 °C. At the time of inclusion, the time of post-dose peripheral blood (plasma sample) extraction for the ivermectin population PK will be randomly assigned to 8 different points: 1.5, 3, 4, 5, 6.5, 24, 48, and 72 h after treatment (see Table 1).

Patients will be treated with 200 mcg/kg ivermectin (3 mg tablets, Exeltis Laboratory, Madrid, Spain) in a single dose: <50 kg (9 mg), 50–64.9 kg (12 mg), 65–79.9 kg (15 mg), 80–94.9 kg (18 mg), >95 kg (21 mg). Treatment will be directly observed at the hospital or by videocall. Forty-eight hours after the administration of the drug, investigators attempt make a phone call to inquire about possible adverse events using a structured questionnaire. In case of presenting relevant adverse events, the patient could be referred for clinical and analytical evaluation (at treating physician discretion). Follow-up visits will take place 3 and 6 months after treatment and will include the following assessments: Hemogram, *S. stercoralis* serology, coproparasitological study and *Strongyloides* specific culture (in case they were positive at baseline). In addition, a serum sample (for sample repository) and a fresh stool sample (for sample repository and *S. stercoralis* PCR determination) will be collected and stored at −80 °C at both visits. 

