The strongyloidiasis diagnosis and follow-up in the ImmunoStrong study is mainly based on serological techniques, which is closer to real-life conditions. Some concerns could arise regarding the sensitivity of serological techniques in immunosuppressed patients, and this fact could affect the patients’ recruitment of the IS group. Regarding specificity issues of the serological techniques, it has been suggested that increasing the cut-off value for positive serology may increase the specificity of the serological test in the diagnosis of confirmed strongyloidiasis [19]. For this reason, patients included in the ImmunoStrong study must have an OD index equal to or greater than 2 in the ELISA test at the time of diagnosis in the absence of larvae detection in parasitological techniques. 

Novel molecular-based diagnostic techniques for strongyloidiasis diagnosis have been developed in the last decades to achieve the highest sensitivity and specificity. A recent meta-analysis, which included 14 studies, evaluated the accuracy of molecular biology techniques for the diagnosis of *S. stercoralis* infection, showing very high specificity of the PCR technique. However, sensitivity showed unsatisfactory results regardless of the reference test used [20]. Moreover, among the 14 included studies, only 1 was performed in immunosuppressed patients, showing scarce benefits of PCR techniques compared with classical parasitological techniques in patients with oncologic diseases [21]. This gap of information will also be covered by the ImmunoStrong study, which will compare the PCR technique with classical parasitological techniques and serology for the strongyloidiasis diagnosis and follow-up after treatment, both in immunocompetent and immunosuppressed patients.

Finally, the present study will perform an ivermectin population pharmacokinetics among the included patients. The information of this sub-study among immunosuppressed patients could be crucial, since this population is usually under a broad range of treatments that could affect the ivermectin concentrations in blood, subsequently affecting the potential efficacy of the single-dose strategy. 

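### Recent ivermectin is excluded but recent albendazole is not, so the effect of an earlier albendazole course can be attributed to the study dose, in a direction that depends on how exposure is spread over the groups

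*Protocol article*

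**What the plan says.** The Introduction describes drug treatment as "basically limited to two drugs: Ivermectin and albendazole", and summarises the trials of the two drugs as "showing a cure rate of 76–98% for ivermectin and of 38–78% for albendazole".

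Section 2.1 opens its list with "The exclusion criteria will be as follows". The only prior-treatment item in that list is "previous treatment with ivermectin (in the last year before inclusion". Albendazole is not named there or anywhere else in the Methods.

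The same section allows the diagnosis to be made either by direct parasitological methods or "by positivity of a serological technique (ELISA) with an optical density (OD) index greater than or equal to 2". The Discussion confirms that "diagnosis and follow-up in the ImmunoStrong study is mainly based on serological techniques".

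Section 2.2 defines cure as a negative direct parasitological test together with "negative *S. stercoralis* serology or decrease of at least 50% of OD index at 6 months after treatment administration". Section 2.3 limits the follow-up stool work to "coproparasitological study and *Strongyloides* specific culture (in case they were positive at baseline", and footnote c of Table 1 says the same.

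Table 1 collects demographic and clinical information, concomitant medication and a directed anamnesis at screening. No eligibility or analysis rule in the article uses prior albendazole.

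**The concern.** The plan recognises that earlier treatment can distort the outcome, because it sets a one-year look-back for ivermectin. It sets none for the other drug that it describes as active.

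For a patient who enters on serology alone, the gap is not closed later. No larvae are needed at entry, stool tests are not repeated, and cure is judged on the change in antibody level. The cure definition accepts a 50% fall in the OD index without seronegativity, so it presumes that a cured patient may still be seropositive. A patient cured by albendazole shortly before enrolment may therefore still have an OD index of 2 or more. Whatever the antibody does next is read as the result of the study dose.

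At stake is the primary noninferiority comparison of immunosuppressed (IS) with immunocompetent (IC) patients. Pre-cured patients in both groups pull the two cure rates together. Pre-cured patients mainly in one group move the difference up or down. The groups are not randomised, so nothing in the design balances this exposure.

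**Working it through.** **Inputs from the protocol article.** IC cure rate 85%, one-sided α 5%, power 80%, margin 14 points and 10% non-evaluable (section 2.6); albendazole cure rate 38–78% (Introduction).

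**Assumptions, not in the article.** The exposure f (share of enrolled patients with recent albendazole), and the probability m that a pre-cured patient meets the cure definition at month 6.

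**Step 1. Reproduce the sample size.** n = (1.645 + 0.842)² × 2 × 0.85 × 0.15 / 0.14² = 80.4, so 81 evaluable per group; 81 / 0.90 = 90 enrolled per group. This agrees with the article's 90 IS and 90 IC patients, and the point made here does not change it.

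**Step 2. Model.** The pre-cured share is k = f × c, with c = 0.38 to 0.78. The observed cure rate is p(1 − k) + k·m, where p is the true ivermectin cure rate. If both groups have the same k and m, the observed difference is (1 − k) times the true difference.

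**Step 3. True difference at the margin.** p = 0.71 (IS) and 0.85 (IC). The probability of declaring noninferiority is found by exact binomial enumeration with the one-sided 95% Wald bound and 81 per group. With no exposure it is 5.2%.

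**Step 4. Upper-bound case, m = 1.** Example with f = 10% in both groups and c = 0.78: k = 0.078; IS = 0.71 × 0.922 + 0.078 = 0.733; IC = 0.85 × 0.922 + 0.078 = 0.862; difference 12.9 points instead of 14.

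| Exposure | False noninferiority rate (c = 0.38 to 0.78) |
|---|---|
| none | 5.2% |
| 1–2%, both groups | 5.3–5.5% |
| 5%, both groups | 5.6–6.2% |
| 10%, both groups | 6.1–7.3% |
| 20%, both groups | 7.3–10.4% |
| 10%, IS only | 7.3–10.2% |
| 10%, IC only | 4.3–3.5% |

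**Step 5. Relax m.** With 10% exposure and m = 0.5:
- Both groups exposed: 6.1–7.1%. The shrinkage factor (1 − k) does not depend on m, so the result barely moves.
- IS only: the observed IS rate is 0.71 × 0.962 + 0.038 × 0.5 = 0.702 at c = 0.38, and 0.71 × 0.922 + 0.078 × 0.5 = 0.694 at c = 0.78. Both are below 0.71, and the error falls to 4.0–3.0%.

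For IS-only exposure the turning point is m = 0.71: above it the error rises, below it the error falls.

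**The case against.** The strongest objection is that nothing in the article shows the exposure occurs. It gives no frequency of prior albendazole use and calls ivermectin the treatment of choice. At 1–2% exposure the effect is negligible. This stands, and it is why the sizes are illustrations over an assumed range.

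Second, using 38–78% as the pre-cured share overstates it. That figure describes patients treated for strongyloidiasis, whereas what matters is the cured share among exposed patients who still qualify. Cured patients have no larvae, and some will have fallen below the OD index of 2, while uncured patients remain eligible. If, as an assumption, half of the cured and all of the uncured remain eligible, 0.38 becomes 0.19 / (0.19 + 0.62) = 0.23 and 0.78 becomes 0.39 / (0.39 + 0.22) = 0.64. This also stands.

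Third, a pre-cured patient has already used up part of the antibody decline and may not halve the OD index again from the study baseline. Such a patient would count as an ivermectin failure. This stands, and it removes any fixed sign when the groups are unequally exposed.

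Fourth, a condensed article may abbreviate eligibility, the study aims at real-life conditions, and a sensitivity analysis could sit in an analysis plan that is not shown. This stands only in part. The criterion is printed with a drug and a time window, so it is not a mere abbreviation, and an analysis plan cannot change who was enrolled. The screening items in Table 1 could capture prior albendazole, but the article does not say that they do.

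A reader might go further and infer that the gap generally favours a noninferiority claim, or that IS patients are the likelier to have had albendazole. The article says nothing about who receives albendazole, and Steps 4 and 5 show error rates below 5.2% under plausible one-sided exposure. Nor does the article say that month 6 was chosen because serology declines slowly; it gives no reason for that time point.

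**Conclusion.** The point holds as a gap in the eligibility criteria with a cheap remedy. One of the two drugs that the article calls active is washed out and the other is not, and for serology-only entrants no later rule separates the effect of an earlier albendazole course from that of the study dose. Patients with larvae at baseline are not affected in this way, since they are not already cured.

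Equal exposure in both groups, with pre-cured patients meeting the cure definition equally often in each, favours noninferiority. The effect is trivial at 1–2% exposure and becomes noticeable from about 10%. Unequal exposure can bias in either direction. All sizes rest on assumed exposure, on a true deficit exactly at the 14-point margin and, except in Step 5, on every pre-cured patient being counted as cured. They do not show that the trial's error rate is in fact inflated. This is an inexpensive improvement, not a defect that undermines the study.

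**What to change.** Extend the prior-treatment exclusion in section 2.1 to albendazole, with the same one-year look-back as for ivermectin.

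If sites object, record prior albendazole (yes or no, and date) at screening, report it by group, and prespecify a repeat of the primary analysis without exposed patients. Reporting by group matters because the direction of any bias depends on the balance.

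The cost is one phrase in the criteria, one medication-history question and a few more screen failures. The sample size stays at 81 evaluable and 90 enrolled per group.

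### HTLV-1 infection is called immunosuppressive in the Introduction, yet under the group definitions such a patient counts as an immunocompetent control

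*Protocol article*

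**What the plan says.** Section 1 (Introduction) explains why these patients matter: "Under immunosuppressive conditions such as corticosteroid therapy, solid organ transplantation, or human T lymphotropic virus 1 (HTLV-1) infection" can amplify autoinfection and lead to severe disease.

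Section 2.1 then fixes the two groups. The IS group is a closed list: "Patients included in the IS group will be defined by presence of any of the following conditions at enrollment". The list opens with a steroid criterion, "Treatment with corticosteroids at a cumulative dose greater than or equal to 20 mg/day of prednisone (or equivalent) for at least 10 days". It continues with cytotoxic drugs or antimetabolites, transplantation and biological drugs, and ends with "active solid or hematological neoplasia, HIV infection with CD4 lymphocyte count below 200 cells/mm^3". HTLV-1 is not on it. For the controls, "patients included in the IC group must not have any of the previous conditions (and no HIV infection regardless of the CD4 lymphocyte count"). The general exclusion criteria in the same section do not mention HTLV-1 either.

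Baseline laboratory work in Section 2.3 includes "HIV serology, and detection of microfilaria in peripheral blood to screen for loiasis in patients coming from endemic areas". Neither that section nor Table 1 names an HTLV-1 test. Table 1 does record concomitant medication at screening, day 0, the PK day and day 2.

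Section 2.2 makes group membership the basis of the primary analysis: "The primary outcome will be noninferiority of the cure rate of immunosuppressed patients compared to immunocompetent patients", with a margin of 14 percentage points.

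**The concern.** The study is observational, so the definitions in Section 2.1 are all that separates the two groups. For HIV they leave a buffer: a patient with a CD4 count of 200 or more and no other listed condition enters neither group. HTLV-1 has no such buffer, although the article itself names it as immunosuppressive. A patient with HTLV-1, no listed condition and no HIV is therefore classed as immunocompetent.

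This matters more in a noninferiority comparison than in a superiority one. Control patients who respond like the test group pull the two observed cure rates together, and here a smaller difference is the result that counts as success. The error at stake is a declaration of noninferiority when IS cure is in truth worse by the margin or more.

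A smaller wording problem lies on the same group boundary. The steroid criterion calls the dose cumulative but states it per day, and eight sites have to apply it.

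**Working it through.** **Inputs from the article.** Cure rate 85% in IC, one-sided α 5%, power 80%, at most 10% non-evaluable, 90 patients per group (Section 2.6); margin 14 points (Sections 2.2 and 2.6).

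**Inputs not in the article (assumed).** The share f of IC patients with HTLV-1, varied from 2% to 10%, and their cure rate, set equal to the IS rate.

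**Step 1: reproduce the planned size.** With equal true rates of 85%:

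n = (z₀.₉₅ + z₀.₈₀)² × 2 × 0.85 × 0.15 / 0.14² = (1.645 + 0.842)² × 0.255 / 0.0196 ≈ 80.4, so 81 evaluable per group.

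81 / 0.90 = 90, which matches the plan. Power at 81 per group is 80.2%.

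**Step 2: dilute the control group.** The observed IC rate is p_C = (1 − f) × 0.85 + f × p_IS, so the observed difference is (1 − f) times the true one. The probability of declaring noninferiority is

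P = Φ[(0.14 − (p_C − p_IS)) / SE − 1.645], with SE = √[p_C(1 − p_C)/81 + p_IS(1 − p_IS)/81].

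**Step 3: at the noninferiority boundary.** The true rates are 85% and 71%, a 14-point deficit.

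| Share f | Controls affected, of 81 | Observed IC rate | Observed difference | P(declare noninferiority) |
|---|---|---|---|---|
| 0 | 0 | 85.0% | 14.0 points | 5.0% |
| 2% | about 1.6 | 84.7% | 13.7 points | 5.5% |
| 5% | about 4 | 84.3% | 13.3 points | 6.2% |
| 10% | about 8 | 83.6% | 12.6 points | 7.6% |

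Worked line for f = 10%: SE = √(0.836 × 0.164/81 + 0.71 × 0.29/81) = 0.0651; (0.14 − 0.126)/0.0651 = 0.215; 0.215 − 1.645 = −1.430; Φ(−1.430) = 7.6%.

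**Step 4: at other true deficits, f = 10%.**

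| True deficit | P with f = 0 | P with f = 10% |
|---|---|---|
| 20 points | 0.5% | 1.3% |
| 5 points | 44.7% | 47.6% |
| 0 points | 80.2% | 80.2% |

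With no true deficit the share makes no difference at all.

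**The case against.** The best defence is that nothing in the article shows a bias. The Introduction links these conditions to amplified autoinfection and severe disease, not to failure of ivermectin in uncomplicated infection. Section 2.1 excludes hyperinfection and dissemination. The Discussion expects similar efficacy in the two groups when those forms are absent, and with equal cure rates dilution does nothing. The share of HTLV-1 among controls may also be small, in which case the effect is about one percentage point of error or less.

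Most of this stands and limits the size of the point. It does not remove the contradiction: equal cure is what the study sets out to test, so it cannot excuse a control definition that conflicts with the article's own statement. Nor is this a detail left to a fuller protocol, because Section 2.1 spells out both groups, down to the extra HIV rule for controls.

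Three stronger readings are tempting and are not supported.

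- **That steroid users below the cut-off are also patients whom the article calls immunosuppressed.** The Introduction mentions corticosteroid therapy without dose or duration, and Section 2.1 then sets a working threshold. Any threshold leaves someone just below it. That is not a contradiction.
- **That the bias has a known direction.** It runs toward noninferiority only if IS cure is truly lower and the misplaced controls share that lower rate.
- **That false noninferiority reaches 8% to 13%.** Those figures (8.4% at a 5% share, 13.2% at 10%) need the misplaced controls to cure at 50%, well below the 71% used for IS at the boundary. The article gives no basis for 50%.

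**Conclusion.** The point holds for HTLV-1. Section 1 and Section 2.1 disagree, and the rule as written places a condition that the article names as immunosuppressive in the immunocompetent arm of the primary comparison.

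The statistical consequence is conditional and probably modest: at the 14-point boundary, the one-sided error goes from 5.0% to about 5.5%, 6.2% or 7.6% at shares of 2%, 5% or 10%. This rests on 81 evaluable patients per group, an 85% cure rate in truly immunocompetent controls, and misplaced controls who cure at the IS rate of 71%. The article does not give the share, and there is no bias if the two groups cure equally.

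For steroid exposure below the cut-off, the documents justify a check on robustness, not a finding of misclassification. The steroid wording needs reconciling in its own right.

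**What to change.** 1. **HTLV-1.** Reconcile Section 2.1 with the Introduction by stating that patients with known HTLV-1 infection do not enter the IC group. They can be listed as IS or kept out of both groups, as already happens for HIV with a CD4 count of 200 or more and no other listed condition.
2. **Steroid exposure in controls.** Prespecify a sensitivity analysis of the primary outcome that leaves out IC patients on any systemic corticosteroid. Table 1 already records concomitant medication, so no new procedure is needed. A blanket exclusion of all steroid users from IC is not required. No rule is needed for lower doses of the other listed drugs, because Section 2.1 sets no threshold for them and any current use already bars a patient from IC.
3. **Steroid criterion.** Reword it so that the cumulative and per-day elements agree and all eight sites apply one reading. Which reading is meant is for the investigators to say.

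**Cost.** This is a change of eligibility wording and one added analysis; the planned 90 per group is unchanged. A few controls are lost, and the sensitivity analysis will be somewhat less precise than the main one. Limiting the rule to known infection leaves undiagnosed HTLV-1 among the controls, because no test is planned. That should be stated as a limitation.
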